### 2.4. Randomization and Blinding

According to a stratified block randomization method, the PRCO PLAN function of the analysis system of SAS software (SAS Institute, Inc., Cary, NC, USA) was used to generate the random number grouping table according to the number of cases and the random proportion of the participating units. There are 5 centers and 4 groups (high-dose group, middle-dose group, low-dose group, and control group), and each group is divided into two layers in a 1 : 1 ratio, while one layer is aged between 45 and 60 years and the other layer is aged between 61 and 75 years. So each group in one single center will recruit 12 patients, with 6 patients between 45 and 60 years old and 6 patients between 61 and 75 years old. Eligible patients are randomly allocated to the high-dose group, middle-dose group, low-dose group, or control group in a 1 : 1 : 1 : 1 ratio. The randomization sequence was generated by the Health Statistics Department of the Fourth Military Medical University of China, which is independent of the trial. The details of randomization sequences are unknown to researchers and outcome assessors who participate in the study and kept in two copies in an opaque, sealed, and stapled envelope that will be kept concealed until the end of the outcome assessment.

The blinding codes are preserved and protected separately by West China Hospital and the other four participating centers. Emergency letters are prepared by a statistician in which the random code and group assignment are included. If the blind code is exposed, the corresponding patient will be excluded. Any of the following situations could call for a blind breaking and urgent measure: a serious adverse event, serious complication, or deteriorative condition.

Following the blinding principle, the five participating centers are isolated from the sponsor unit during the study and they will contact only the supervision agency (Beijing Chuangli Medical Technology Development Co., Ltd., China), which is responsible for contacting participating centers and monitoring the progress of research but is blind to group assignment.

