#### 2.6.5. Primary Outcomes

*Duration of All Symptoms*. Duration of all symptoms is defined as the number of days from enrollment to the day that all symptoms disappear (the time from the symptom severity score above zero until 2 days of the severity score marked as zero). If symptom severity is marked above zero on the day after a single day of zero, the cold is defined as continuing. If the day marked above zero is the 11th day, this is defined as the end of the cold, but if symptoms last more than 11 days, follow-up will continue via phone call or e-mail until all symptoms are absent. The first day of medication administration is defined as the 1st day (day 1) in the study. The start of the day is defined as 6:00 a.m., and symptoms absent before 6:00 a.m. are regarded as occurring the day before.

Because all the participants in the trial have Qi-deficiency syndrome and normally present certain Qi-deficiency symptoms (fatigue, shortness of breath, and spontaneous perspiration), we define the disappearance of Qi-deficiency symptoms (symptom score = 0) (Table 2) as all the symptoms returning to the basic level present before the onset of common cold.

*The Total Score Reduction of Jackson's Scale*. Jackson's scale [27], which is specific for diagnosis and symptom severity assessment of common cold, contains 8 symptoms (sneezing, headache, malaise, chilliness, nasal discharge, nasal obstruction, sore throat, and cough) and rates as 0 = absent, 1 = mild, 2 = moderate, and 3 = severe. The symptom score will be summed on the 1st day and the 4th, 6th, and 11th days after intervention, and the score reduction will be calculated between the 1st day and the days after the intervention.

The symptom severity and score are assessed by researchers who are blind to the trial, and one participant is assessed by the same researcher consistently throughout trial. Participants will not be allowed to assess their overall illness or level of severity to avoid assessment bias.

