*The Total Score Reduction of TCM Symptoms Scale*. In compliance with the severity measurement of common cold in the Guidelines for Clinical Research of New Chinese Medicine [28], symptom score of CCQDS is obtained from a four-point Likert-type symptom severity scale (Table 2), with different score criteria for main symptoms and secondary symptoms: (1) main symptoms: 0 = no symptoms; 2 = mild; 4 = moderate; 6 = severe; (2) secondary symptoms: 0 = no symptoms; 1 = mild; 2 = moderate; 3 = severe. The total score of TCM symptoms (including main and secondary symptoms) will be summed on the 1st, 4th, 6th, and 11th days, and the score reduction is defined as the scores on the 1st day minus the scores after the intervention, which will be calculated on the 4th, 6th, and 11th days.

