### 2.8. Statistical Analysis

The full analysis set (FAS) is the primary analysis set for efficacy with an intention-to-treat (ITT) principle. In the FAS, all patients will be treated with at least one dose of the study drug and at least one clinical observation will be recorded in the study. All subjects without any major protocol deviations will be involved in the per-protocol set (PPS). The safety analysis will be conducted for randomized subjects who have completed at least one study visit and have safety data. Descriptive statistics will be performed on continuous variables, frequencies, and categorical variables. All symptom durations, total score reductions on Jackson's scale and TCM symptoms, the duration of each TCM symptom, the decreasing rate of TCM main symptoms, and the reduction score of TCM symptoms will be estimated with the Kaplan-Meier technique and compared using the stratified log-rank test. Comparisons among different dose groups and age layers will be conducted with an analysis of variance (ANOVA) and a least significant difference *t*-test. In this multicenter trial, the Cochran-Mantel-Haenszel test stratified by clinical centers and the logistic regression model adjusted for covariates will be used. Statistical analyses will be conducted by an independent statistician from the Health Statistics Department of the Fourth Military Medical University using the SAS statistical software 9.1.3 (SAS, Cary, North Carolina State University, North Carolina, USA).

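### No stated analysis of the primary outcome duration of all symptoms uses the Day 1 symptom score: the stratified log-rank test is valid, but may lose efficiency and leaves chance severity imbalance unadjusted

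*Protocol article*

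**What the plan says.** The first primary outcome is a time to event. In Section 2.6.5, "Duration of all symptoms is defined as the number of days from enrollment to the day that all symptoms disappear", and follow-up continues past Day 11 if symptoms persist. Section 2.8 says that symptom durations "will be estimated with the Kaplan-Meier technique and compared using the stratified log-rank test". It does not name the strata.

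Entry severity is recorded on both scales. For Jackson's scale, "The symptom score will be summed on the 1st day and the 4th, 6th, and 11th days after intervention". For the TCM scale, "The total score of TCM symptoms (including main and secondary symptoms) will be summed on the 1st, 4th, 6th, and 11th days". Table 3 schedules symptom scoring at Visit 1 for every patient, and Section 2.6.6 describes the Day 1 main-symptom and secondary-symptom scores as taken before the intervention.

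Section 2.4 stratifies randomisation by centre and by age: "each group is divided into two layers in a 1 : 1 ratio, while one layer is aged between 45 and 60 years", and the other covers 61 to 75. Severity is not a stratum.

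Section 2.8 names three further methods: ANOVA with least significant difference t-tests for dose groups and age layers, a Cochran-Mantel-Haenszel test stratified by centre, and a model with covariates, "the logistic regression model adjusted for covariates will be used". It does not say which outcomes or covariates that last model covers.

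**The concern.** The outcome ends only when the last symptom has gone. A patient who enters with more symptoms, or worse ones, may plausibly take longer to get there. If so, Day 1 severity explains part of the variation in duration, and an analysis that ignores it leaves that variation in each dose-versus-control comparison as noise.

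The methods listed do not fill this gap for a duration. ANOVA is named without a baseline covariate, logistic regression needs a binary outcome, and the Cochran-Mantel-Haenszel test is stratified by centre.

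The stakes are power for each contrast and the clarity of the dose ranking. With 50 to 60 patients per arm, severity is balanced only by chance, and the trial is meant to identify an optimal dose among three. The point concerns duration only, not the score reductions.

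**Working it through.** **The plan's own figure.** Section 2.3 gives two-sided alpha 0.05, 90% power, 50 per group, and 60 after allowing for 20% loss. The 50 cannot be reproduced, because the article states no outcome, effect size, SD or hazard ratio. The 60 is 50 × 1.20. The totals agree: 4 × 60 = 240 and 5 × 48 = 240.

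**Effect implied by 50 per group**, assuming that the 90% applies to duration:
- Standardised difference: d = (1.960 + 1.282) × √(2/50) = 0.648.
- Hazard ratio, if all 100 patients in a pairwise comparison resolve: exp(2 × 3.242/√100) ≈ 1.91.

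**Linear approximation.** Adjusting for a baseline score with correlation ρ to the outcome multiplies the residual variance by 1 − ρ². Power = Φ(d√(n/2)/√(1 − ρ²) − 1.96). With n = 50, d√(n/2) = 3.242.

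| Assumed ρ | Power after adjustment | Equivalent n per arm, 50(1 − ρ²) |
|---|---|---|
| 0 | 90.0% | 50 |
| 0.2 | 91.1% | 48.0 |
| 0.3 | 92.5% | 45.5 |
| 0.4 | 94.3% | 42.0 |
| 0.5 | 96.3% | 37.5 |

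A 20% loss from 60 leaves 48 per arm. The starting power is then 88.8%, rising to 91.5%, 93.4% and 95.6% at ρ = 0.3, 0.4 and 0.5.

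**Simulation as a check on direction.** A log-rank test stratified by centre and age was compared with a Cox model using the same strata plus Day 1 severity. Settings: 50 per arm, 10 strata, treatment hazard ratio 1.91 conditional on severity, whole-day durations, assumed median 7 days, assumed censoring at Day 14, 600 runs per setting, Monte Carlo error about 1.6 to 2 points.

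| Severity hazard ratio per SD (assumed) | Log-rank | Adjusted Cox |
|---|---|---|
| 1.0 | 82% | 81% |
| 0.82 | 82% | 80% |
| 0.67 | 75% | 80% |
| 0.55 | 66% | 77% |
| 0.45 | 61% | 78% |

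The conditional effect is held fixed here, so log-rank power falls as severity becomes more prognostic. In the linear approximation the unadjusted power is held at 90%. The two sets of gains are therefore not on the same footing, but they agree in direction: nil when severity is weak, larger as it strengthens.

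Under no treatment effect, rejection rates were 3.7% to 8.0% for log-rank and 2.8% to 6.5% for adjusted Cox, with no consistent difference. The 8.0%, at the strongest covariate, is more than Monte Carlo error alone would suggest and was not rerun.

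**Chance imbalance.** The difference between two arms in mean Day 1 severity has an SD of √(2/50) = 0.20 severity SDs at 50 per arm and √(2/60) = 0.18 at 60. If the severity hazard ratio were 0.67 per SD (log about −0.4), an imbalance of 0.20 would shift the log hazard ratio by roughly 0.4 × 0.20 = 0.08, a factor of about 1.08. That is modest beside 1.91, but it matters more when ranking neighbouring doses.

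**The case against.** The strongest reply is that a stratified log-rank test is a standard and valid choice for a randomised time-to-event outcome, and that a condensed article may leave covariates to an analysis plan. The first part stands. The second is weaker: Section 2.8 commits to a specific test for this outcome. If an analysis plan specifies an adjusted model, the two texts need to be aligned.

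Three stronger readings are tempting, and the article does not support them.

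- A reader might infer that the log-rank test is the only comparison and cannot use severity at all. The strata are unnamed and could include severity categories, and ANOVA is also listed for dose groups with no outcome attached. What holds is narrower: the test cannot take the continuous score, and no stated method is said to adjust duration for it. Adding severity categories to 5 × 2 = 10 centre-by-age strata, each with 240/10 = 24 patients and 6 per arm, would also make the strata sparse.
- A reader might infer that chance imbalance makes the result invalid. Randomisation already accounts for it in the type I error rate. Imbalance affects precision and the estimate in the particular sample.
- A reader might take the scale limits (Jackson 2 to 24, TCM total up to 4 × 6 + 5 × 3 + 1 = 40) as the spread among patients. The syndrome criteria in Section 2.2.1 set a floor of about 2 + 2 + 2 + 1 + 1 + 1 = 9 on the TCM scale if the three secondary symptoms are scored ones. The Discussion says that patients with severe symptoms are excluded. A narrower range tends to lower the correlation.

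It is also fair that prognostic strength is assumed. Patients enter within 48 hours of onset, and the Introduction puts the symptom peak at 1 to 3 days, so the Day 1 score partly reflects timing on a rising curve.

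**Conclusion.** The point holds as one of efficiency and of protection against chance imbalance. Section 2.8 fixes a valid test for a primary outcome and states no analysis of that outcome that uses a baseline score already collected from everyone.

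The size cannot be settled from the article. It rests on two assumptions: that the 90% power with 50 per group refers to duration, and a value for the severity-duration correlation. On the linear approximation the gain is about 1 point at 0.2, 2.5 at 0.3, 4.3 at 0.4 and 6.3 at 0.5. It is nil if severity is not prognostic, and the simulations then show no loss beyond simulation error. The change is worth making because it costs so little, not because a large loss has been shown.

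**What to change.** In Section 2.8, before unblinding, prespecify for duration of all symptoms a Cox proportional hazards model with treatment group and the continuous Day 1 total TCM score as terms, stratified by centre and age layer. Report the hazard ratio and 95% CI for each dose against control, which also gives the effect estimate that dose selection needs and the log-rank test does not supply. Keep the Kaplan-Meier curves and the stratified log-rank test as the supporting unadjusted analysis, and name its strata.

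The TCM total is suggested over Jackson's because it covers more of the symptoms that must resolve, such as shortness of breath, expectoration and spontaneous perspiration. This is a judgement; what matters is that one score is fixed in advance.

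The cost is a sentence or two in the analysis section, with no new data, visits or patients. The downside is small: the model assumes proportional hazards, and its hazard ratio is conditional on severity. The retained curves and log-rank test let readers judge both.

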**Methods/Design:**

This is a multicenter, randomized, double-blind, placebo-controlled, phase II clinical trial. A total of 240 eligible patients will be recruited from five centers. Patients are randomly assigned to high-dose group, middle-dose group, low-dose group, or control group in a 1 : 1 : 1 : 1 ratio. All drugs are required to be taken 3 times daily for 5 days with a 5-day follow-up period. Primary outcomes are duration of all symptoms, total score reduction on Jackson's scale, and TCM symptoms scale. Secondary outcomes include every single TCM symptom duration and score reduction, TCM main symptoms disappearance rate, curative effects, and comparison between Jackson's scale and TCM symptom scale.

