### 2.3. Sample Size Calculation

The sample size was determined using Encyclopaedia Medical Statistics 3.2 software (PEMS 3.2, Guangzhou Jing far Pharmaceutical Research Co., Ltd., Guangzhou, China) with 90% power and a significance level of 0.05 (two-sided). According to Lizogub et al. [30], the sample size should consist of 50 participants in each group. Considering the potential 20% loss, 60 participants are needed for each group. As there is a low-dose group, a middle-dose group, a high-dose group, and a control group with five centers involved, a total of 240 participants will be recruited in this study, with 48 patients recruited at each center.

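### Dose comparisons on three unranked primary outcomes are unadjusted, and the named LSD test lacks strong familywise control with four groups

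*Protocol article*

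**What the plan says.** All references are to the protocol article.

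- **Groups** (Section 2.4). Patients are "randomly allocated to the high-dose group, middle-dose group, low-dose group, or control group in a 1 : 1 : 1 : 1 ratio", which gives three dose-versus-control contrasts and six pairs in all.
- **Primary outcomes** (Abstract and Section 2.6.5). "Primary outcomes are duration of all symptoms, total score reduction on Jackson's scale, and TCM symptoms scale". No order is given, and no rule says whether one outcome or all three must succeed.
- **Timing** (Section 2.6.5). Score reductions are taken from day 1 to each later visit; for the TCM scale the text adds "which will be calculated on the 4th, 6th, and 11th days", and the Jackson scale uses the same days. No day is named as primary. Duration is a single quantity with no assessment days.
- **Tests** (Section 2.8). The durations and both total score reductions are assigned to Kaplan-Meier estimation and a stratified log-rank test. A separate sentence reads "Comparisons among different dose groups and age layers will be conducted with an analysis of variance (ANOVA) and a least significant difference" t-test. It names no outcome and does not say whether LSD follows only a significant ANOVA. A Cochran-Mantel-Haenszel test and logistic regression are also mentioned.
- **Significance level** (Section 2.3). The only level given is 0.05 two-sided, with 90% power, as an input to the sample size.

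**The concern.** LSD is a set of ordinary t-tests at the nominal level. Gated on a significant ANOVA, it holds the error rate for one outcome in two situations: when no group differs, or when there are only three groups. With four groups, one effective dose is enough to make the F-test significant. The other three groups are then compared with no protection. The log-rank route has the same gap if it is read dose by dose.

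On top of this come three primary outcomes, two of them on three days, with no order. A reader of the results could pick any outcome, day and dose that reached 0.05 and call it a primary finding.

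What is at stake is the trial's own claim. The Discussion promises robust evidence on efficacy and on the optimal dose. An ineffective dose that appears to work alongside an effective one is the error that misleads dose selection, and Section 2.2.2 expects the trial to inform phase III.

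**Working it through.** **1. The plan's own figure.** Section 2.3 says "the sample size should consist of 50 participants in each group" but gives no effect size or SD, so 50 cannot be reproduced. It can be back-solved for one two-group comparison:

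d = (1.960 + 1.282) × √(2/50) = 3.242 × 0.2 ≈ 0.648.

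This is an assumption, used only for the cost of the fix. The 60 recruited per group equal 50 × 1.2. After a 20% loss, 60 × 0.8 = 48 per arm remain.

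**2. Number of primary dose-versus-control tests.** (1 duration + 2 scores × 3 days) × 3 doses = 7 × 3 = 21.

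**3. Benchmark if tests were independent,** 1 − 0.95^k:

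- k = 3: 14%
- k = 9 (three outcomes, one day each): 37%
- k = 21: 66%

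The tests are correlated, so these overstate the rate.

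**4. Simulation with no effect of any dose.** Four equal arms with a shared control, seven correlated normal statistics, significance at |t| > 1.96, and 200,000 replicates. The documents give no correlations. The assumed ranges are 0.7-0.9 for the two scales on the same day and 0.4-0.7 otherwise. The entries give the chance of at least one significant dose-versus-control result.

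| Counting | No F gate | LSD gated on F |
|---|---|---|
| Either direction | 37-50% | 14-20% |
| Favouring SGLNG only | 19-26% | 7-10% |

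The lower end of each range belongs to the higher correlations. With one common correlation from 0 to 0.9 among all seven, the either-direction figures run from 60% down to 26% ungated and from 25% down to 10% gated.

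**5. One outcome only.**

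- No dose works, no gate: about 12.5% over the three contrasts with control.
- No dose works, F gate: about 5% over all pairs, so here the gate does its job.
- One dose works strongly, gate or no gate: about 12% over the three pairs among the remaining equal groups, and about 9% for the two ineffective doses versus control.

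**6. All seven outcome-days, one dose working on all of them,** common correlation 0.5, F gate: 38% chance that an ineffective dose is significant against control on at least one.

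**7. Log-rank.** With equal arms and a shared control, pairwise log-rank statistics have about the same joint distribution under no effect as the t-statistics in step 5. Three unadjusted comparisons therefore also give about 12.5% on one outcome.

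**The case against.** Several objections are fair, and some limit the point.

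- *LSD is not the only method named.* Correct. Section 2.8 sends the primary outcomes to the stratified log-rank test, and the LSD sentence names no outcome. That does not remove the problem, because the log-rank comparisons are unadjusted too. It does mean that replacing LSD alone would leave part of it in place.
- *The F-test protects LSD.* Since ANOVA is named first, the gated reading is natural. It protects one outcome when no dose works. It does not protect across seven outcome-days, or once one dose works.
- *A false success is likely when SGLNG does nothing.* A reader might infer this from the ungated 37-50%. The documents do not support it. Under the gated reading the figure is 14-20%, and it includes doses significantly worse than placebo. In the favourable direction it is 7-10%.
- *The trial breaks a promised 5% familywise rate.* A reader might infer this as well. The 0.05 is a sample-size input, and no familywise rate is stated.
- *Three outcomes, three days and three doses make 27 tests.* Duration has no assessment days, so the maximum is 21. The article does not declare each day a separate confirmatory test, so 21 is an upper count of what can be read at 0.05.
- *An order or alpha split may stand in a full protocol or SAP.* It may, and silence alone would be no finding. But the article fixes LSD for four groups, and a later plan would have to replace that, not just add detail.
- *This is phase II.* Strict control matters less in exploratory work. The article nevertheless claims robust evidence on efficacy and the optimal dose, and dose selection is where LSD fails.
- *All three outcomes might be required.* That would remove the part due to several outcomes. No such rule is stated, and the part due to several doses would remain.

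**Conclusion.** The plan names an unadjusted procedure that lacks strong familywise control for four groups, and leaves three primary outcomes without an order and two of them without a primary day.

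With no true effect, the two-sided error over the primary family is about 3 to 4 times 5% if LSD is gated (14-20%) and about 7 to 10 times if it is not (37-50%). In the favourable direction, 7-10% gated compares with 2.5% for a single two-sided test. These figures rest on assumed correlations and approximately normal statistics. No correlation tried brings the 21-test family back to 5%.

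The single-outcome result needs no assumption about correlation between outcomes: once one dose clearly works, about 12% false positives among the other three groups. This bears most directly on the optimal-dose conclusion. It should be settled before unblinding.

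**What to change.** Change the wording of Sections 2.6.5 and 2.8 before unblinding:

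1. State a testing order for the three primary outcomes, for example the order already listed: duration, Jackson, TCM.
2. Name one confirmatory day for both scores. Day 6 is one option; it is already scheduled and is the first visit after the 5-day course.
3. Within each outcome, replace LSD with Dunnett's test against control, or test the doses in a fixed high-middle-low sequence.
4. Apply the same sequence, or a Dunnett- or Holm-type adjustment, to the pairwise stratified log-rank tests, and say which test is primary for each outcome.
5. Write down when testing passes from one outcome to the next. The simplest rule is a single chain that stops at the first non-significant result.
6. Label the other days, the dose-versus-dose pairs and the age-layer comparisons as supportive.

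**Cost.** No extra visits or data are needed. With d = 0.648 (back-solved, since the article gives no effect size) and 48 per arm, the standardised signal is 0.648 × √(48/2) ≈ 3.18. Unadjusted power per comparison is Φ(3.18 − 1.96) ≈ 89%. With Dunnett's critical value of about 2.35-2.37 it is about 79-80%. A fixed sequence keeps full alpha for the first test, but a failure there blocks every claim further down the chain.

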#### 2.2.2. Inclusion Criteria

Inclusion criteria are that participants are aged between 45 and 75 years; have symptoms of Qi-deficiency in normal times such as fatiguing easily, poor appetite, or suffering more frequent colds (≥6 times/year) when seasons and climates change; meet the diagnostic criteria of a common cold within 48 hours of onset; meet the diagnostic criteria of CCQDS; and possess an understanding of the trial procedure and a willingness to sign the consent form.

Although the name of the medication indicates that its possible target population might be the “elderly people,” based on the TCM pathology of common cold with Qi-deficiency, patients with younger age than the elderly patients may also present CCQDS. Therefore, in the RCT to assess the clinical efficacy of SGLNG, we extend the age of the study population from 45 to 75. This may provide broader target population for the medication and also provide evidence for phase III study in the future.

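### As worded, the planned ANOVA and LSD comparison of age layers tests whether age affects recovery; it does not show whether the SGLNG effect is consistent across the two randomised age layers

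*Protocol article*

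**What the plan says.** - **Analysis (Section 2.8).** The only statement on age is "Comparisons among different dose groups and age layers will be conducted with an analysis of variance (ANOVA) and a least significant difference" t-test. It names no dose-by-age term and no contrast with control inside a layer. The section also mentions a stratified log-rank test without naming the strata, a Cochran-Mantel-Haenszel test stratified by centre, and a logistic regression with unnamed covariates.
- **Randomisation (Section 2.4).** Age is a stratification factor: "each group is divided into two layers in a 1 : 1 ratio, while one layer is aged between 45 and 60 years", the other being 61 to 75. Cell sizes are fixed by centre: "So each group in one single center will recruit 12 patients, with 6 patients between 45 and 60 years old" and 6 in the older layer. No reason for stratifying by age is given.
- **Age range (Section 2.2.2).** The product name suggests elderly patients, but "we extend the age of the study population from 45 to 75". The stated benefit is tentative: "This may provide broader target population for the medication and also provide evidence for phase III study in the future".
- **Trial question (Section 4).** It is whether SGLNG reduces symptoms and which dose is best. Age is not mentioned.

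**The concern.** Comparing layers and comparing treatment effects between layers are different contrasts. The first asks whether patients aged 61-75 improve more or less than those aged 45-60, whatever they were given. The second asks whether the gap between SGLNG and control changes with age. Only the second bears on whether the younger patients brought in by the wider age range benefit as the older ones do.

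If the sentence is carried out as written, two things can go wrong. A plain prognostic effect of age gives a significant layer comparison that may be taken as information about the drug. A real difference in drug effect between layers can leave the layer comparison unremarkable. Age layer and centre, the factors used in randomisation, are also not placed as terms in the ANOVA of the dose groups.

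**Working it through.** **Inputs from the article.** Four groups allocated equally, two age layers, five centres, and 6 patients per group per layer per centre (Section 2.4). The sample size section gives 90% power, two-sided 0.05, 50 per group before loss and 60 per group after 20% is added (Section 2.3).

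**The plan's own total.** 6 × 2 layers × 4 groups × 5 centres = 240, which agrees with 60 × 4 and 48 × 5. Each group has 6 × 5 = 30 patients per layer as randomised. If the 50 evaluable patients split evenly, it has 25.

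**Implied effect (assumption).** The article gives no effect size, SD or rate behind its 50 per group. For a continuous outcome, the normal approximation inverts to

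d = (1.960 + 1.282) × √(2/50) = 0.648 SD.

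**Do the two contrasts answer the same question?** A two-way layout of 4 groups × 2 layers with 30 per cell was simulated 4,000 times per scenario. The age main-effect F test (1 df) was compared with the dose-by-age F test (3 df), each at 5%.

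| Scenario | Age test significant | Interaction test significant |
|---|---|---|
| Older layer 0.5 SD lower in every group; no interaction | 97% | 4% |
| All doses work (0.648 SD) in the younger layer only; overall layer means equal | 5% | 41% |

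In the first row the age test responds to prognosis alone. In the second it stays at its null rate although the drug works in one layer only.

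**Power of the replacement test, one dose against control.** The contrast is a difference of two differences among four cell means, so SE = SD × √(4/n).

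- n = 25: SE = 0.400 SD. Full effect: Φ(0.648/0.400 − 1.96) = 0.367. Half effect: Φ(0.324/0.400 − 1.96) = 0.125.
- n = 30: SE = 0.365 SD. Full effect: 0.427. Half effect: 0.142.
- Interaction detectable with 90% power: 3.242 × 0.400 = 1.30 SD, or 3.242 × 0.365 = 1.18 SD.

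**Illustrations under assumed effects only.**

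- If older patients recover 0.4 SD less, a comparison of 100 with 100 is significant about 80% of the time with no difference in drug effect.
- Taking d = 0.655 (the t-test version of the implied effect), power within a layer of 25 per group is 62.1%. Two layers with the same true effect would then differ in significance 2 × 0.621 × 0.379 = 47% of the time, if someone judged consistency that way.

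**The case against.** The strongest reply is that the sentence does not fix the analysis described here. It could mean a two-factor ANOVA, possibly with an interaction, or dose comparisons within each layer. With only two layers, an LSD step adds nothing to a pooled comparison of layers, which lends those readings some weight. A within-layer analysis would also give SGLNG-control differences by age. The article is a condensation, and a fuller protocol or SAP may settle the model. This stands, and it limits the point to what the sentence says when read literally.

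Three stronger readings are tempting, and the article supports none of them.

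- A reader might infer that randomisation was stratified by age in order to test for a different drug effect by age. No reason is given for the stratification, and balance on a prognostic factor is an ordinary one. Section 2.2.2 explains only why the age range was widened.
- A reader might infer that LSD over all eight dose-by-age cells, 28 pairs, leaves false positives unchecked. Section 2.8 pairs LSD with ANOVA. In the usual procedure LSD follows a significant F test, which holds the error near 5% when no cells differ. LSD can still inflate error when some cells differ, but that is a separate multiplicity matter.
- A reader might take the 80% and 47% figures as error rates of this trial. Detecting a real age difference is not an error, and the article nowhere says that layers will be judged by which one reaches significance.

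It is also fair to say that an interaction test at this size cannot settle the question. What the reply does not remove is that a method for age is stated, and that under its plain reading it does not address consistency of effect.

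**Conclusion.** The point holds in a limited form. Read literally, Section 2.8 tests the prognostic effect of age, and that contrast cannot inform the target-population aim in Section 2.2.2. The simulation shows that the gap can run both ways: 97% against 4% when only prognosis differs, and 5% against 41% when only the drug effect differs. These figures depend on the assumed 0.5 SD and 0.648 SD effects, normal data and 30 per cell; the difference between the two contrasts does not.

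The article does not tie any phase III decision to this comparison, so it would go too far to say that the decision will rest on the wrong contrast. The defect is one of specification. It is worth correcting because the better analysis uses data and strata that the trial already has.

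**What to change.** Replace the sentence for the score-reduction outcomes:

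1. Fit a model with dose group plus the randomisation factors, age layer and centre.
2. Remove the LSD comparison between age layers. In its place, test the dose-by-age-layer interaction and label it exploratory.
3. Report each dose's difference from control within each layer with a 95% CI. Do not judge consistency by which layer reaches significance.

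**Cost.** A sentence or two of analysis wording, with no extra patients, visits or data. The drawback is low power for the interaction, as shown above. A non-significant result must not be read as proof of a consistent effect. The within-layer intervals will be wide: at the assumed cell sizes the half-width is about 1.96 × √(2/25) = 0.55 SD, or 1.96 × √(2/30) = 0.51 SD. The age analysis should be described as supportive evidence for planning phase III and nothing more.
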